### Intervention

Based on previous studies [5, 17, 23], seven sessions of r-TMS will be administered over 15 days [17]. In detail, the parameters used in each session will be:
International 10/20 system for the location of the target area (non-lesioned left posterior parietal cortex);60% power;Frequency: 1 Hz; andNinety pulse trains with ten pulses each (total 900 stimuli) resulted in a whole stimulation period of 15 min.

The stimulation coil will be positioned tangentially on the target area. Each r-TMS session will last 15 min and be administered every other day (e.g., Monday-Wednesday-Friday, Monday-Wednesday-Friday, Monday).

Following the rTMS, the visual scanning treatment will be administered by speech and language therapists and cognitive therapists, who will administer various visual scanning tasks, increase the patient’s awareness of the LHN clinical manifestations, and teach the participant strategies to improve spatial exploration abilities [23]. In particular, three different training protocols will be used:
Visuospatial training;Reading and copying training; andCopying of line drawings on a dot matrix.

All training protocols include three increasing levels of difficulty, thus giving nine possible test-difficulty combinations. Each level of difficulty will be practiced until the subject will reach a level of accuracy of 75%. The training will be carried out in 50 min sessions for 5 days a week within 15 days [23], for a total of 11 sessions. On the days when the r-TMS is also carried out, the visual scanning protocol administration will follow the brain stimulation.

### Control

In the control group, where a SHAM placebo stimulation is implemented, the stimulation parameters will be the same, but the coil of the r-TMS will be positioned at 90° on the target area. Thus, no specific cortical modulation will be implemented (SHAM stimulation). The visual scanning protocol will be administered with the same modalities and time frame for this group, as detailed for the intervention group. All routine care is permitted for both groups during the study period.

### Outcomes

#### Primary endpoint

The Behavioral Inattention Test (BIT), a neuropsychological battery for visual and cognitive assessment of LHN in standard paper and pencil form, represents the primary outcome. The BIT consists of two subscales (cognitive and behavioral) with standardized scores, where lower ratings indicate a more severe visual-spatial impairment.

#### Clinical secondary endpoints

In this context, subtests from the TAP battery (Test of Attentional Performance) will be administered to test the attention levels of LHN patients. In particular, we will administer the following subtest from the TAP: Alertness and Visual Field/Neglect. The Catherine Bergegò Scale (CBS) assesses specifically the presence and severity of LHN in the activities of daily living (i.e., eating or reading biases). Motricity Index (MI) and Trunk Control Test (TCT) will be used to measure motor impairments, whereas the motor scale of the FIM™ will assess dependence in ADL and mobility. In this way, it will be possible to evaluate different clinical aspects related to LHS and control other improvements induced by the rehabilitation protocol.

#### Neurophysiological secondary endpoints

Finally, in the present study, lateralized visual processing’s neurophysiological correlates are collected to investigate the common interhemispheric imbalance in LHN [1, 10, 28]. In this study, the EEG will be recorded while patients perform a visual detection task (Fig. 2) seated at a distance of 50 cm from the computer’s screen. Patients will be prompted to fix a central fixation cross on a screen while visual stimuli are presented. Stimuli will be small yellow squares (1 cm × 1 cm) shown in a black background to detect color contrast between the stimuli and the background easily. Each trial will start with a white central fixation cross over a black background. Then, after a varying stimulus onset asynchrony between 640 and 960 ms (steps of 80 ms), a stimulus will be presented randomly on the right or the left of the fixation cross on a view distance angle 28° along the midline. Stimuli will be displayed for 96 ms; before the subsequent trial, a black background with the fixation cross will be presented for 1000 ms (Fig. 2). In general, the visual detection task consists of a passive visual task with lateralized stimuli, and participants will be prompted to keep the fixation during all tasks [7, 8]. Whenever participants lose the fixation, feedback will be provided to recover it. Overall, 256 stimuli will be presented in 4 blocks of 64 stimuli, where the overall task will have an average duration of 20 min. The EEG will be recorded from 18 Ag/AgCl-cup electrodes according to the 10/20 system referenced to the linked ear lobes. The EEG signal will be recorded from electrodes: Fz, Cz, Pz, C4, C3, P4, P3, F4, F3, Oz, O1, O2. Impedance for EEG and electrooculogram (EOG) electrodes will be kept below 10 kΩ. Off-line, the amplitude in microvolt (μv), and the latency in milliseconds (ms) of the negative peak of the N100 VEP component will be analyzed separately for left and right-presented stimuli in correspondence of posterior electrodes [8]. Then, indexes of interhemispheric imbalance will be extracted. In particular, here we propose the Visuospatial Attention Bias Index (vABI), which is based on N100 peak amplitude and interhemispheric transmission time (IHTT) [29, 30], which is a further index of hemispheric imbalance, based on N100 peak latency.

**Fig. 2 Fig2:**
[figure not shown]
Visual detection task. Each trial starts with a central fixation cross for a jittered time between 640 and 960 milliseconds (ms), then a stimulus is presented randomly either on the left or on the right of the fixation cross for 96 ms. After stimulus presentation, a fixation cross remains for 1000 ms, and then a new trial starts

Note. The vABI will be calculated as a lateralization index [31] for the N100 amplitude. The vABI will be extracted in two steps. First, N100 for left and right presented stimuli will be calculated in the averaged activity from posterior electrodes (i.e., mean of P3 and P4) to have a signal of the two hemispheric activations after lateralized stimulus presentation. Then, for each participant, the difference in the activations for lateralized stimuli will be calculated as the difference between the resulted N100 peaks for left and right-presented stimuli (i.e., vABI = N100 amplitude for right stimuli − N100 amplitude for left stimuli). Such an index can measure interhemispheric imbalance as it reflects the difference in the activation of the two hemispheres in response to lateralized stimuli. Similarly, based on N100 peak latency, we will compute the IHTT [29, 30], an indicator of the EEG signal’s transmission times from one hemisphere to the other. In particular, we will calculate the IHTT as the difference between the latencies of the negative peak of N100 for left presented stimuli on the posterior electrodes P3 and P4 (i.e., IHTT = N100 latency on P4 - N100 latency on P3), thus constituting a single index in milliseconds of the interhemispheric transmission times specifically for left presented stimuli.

### Sample size

The sample size calculation was based on the results and the population variance from previous studies, which employed the BIT as a primary outcome measure [16, 17, 28, 32]. In particular, we calculated the sample size on the BIT (primary endpoint) using the following formula:
$$ N=\frac{2{\left({z}_{\left(1-\alpha \right)}+{z}_{\left(1-\beta \right)}\right)}^2{\sigma}^2}{\delta^2} $$where *N* is the final sample size; σ^2^: population variance established on previous studies [17] = 3.1; δ^2^: absolute error allowed for parameter estimation = 2.84; *z*: constant (corresponding to the value of the standardized normal random variable) that depends on the level of confidence desired for the estimation, fixing *α* = 0.05 and 1 − *β* = 0.80, (*Z*_1 − *α*_ + *Z*_1 − *β*_)^2^ = 10.5. The sample size resulting from the formula is 25.2. Consequently, the minimum sufficient simple to reach our primary outcome was established as 56 subjects (28 per group), to be enrolled over 2 years, assuming a 10% loss at follow-up.

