## Methods

### Trial design and study design

We present the SMART ATLAS trial (**S**timolazione **MA**gnetica **R**ipetitiva **T**ranscranica nell’**AT**tenzione **LA**teralizzata dopo **S**troke; in English: repetitive transcranial magnetic stimulation in lateralized attention after stroke), a multicenter, randomized, controlled trial with pre-test (baseline), post-test, and 12 weeks follow-up assessments aiming at comparing the efficacy of inhibitory r-TMS, applied over the left intact parietal cortex of LHN patients, followed by visual scanning treatment (VS) [27], in comparison with a placebo stimulation (SHAM control) followed by the same visual scanning treatment, on visuospatial symptoms of LHN in a population of stroke patients. Our methodological approach provides two parallel groups (active r-TMS and SHAM placebo groups) with a 2:2 randomized allocation ratio in a superiority trial design. Figure 1 and Table 1 show the study flowchart and the study time points, respectively.

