Homogeneity vs. heterogeneity: For each outcome measure, the ANCOVA assumption of homogeneity of regression slopes will be verified [38]. In case the assumption is violated, a CHANGE measure (i.e., a score of gain in the specific outcome) will be considered in a 2 × 2 mixed-model ANOVA with the between factor group and the within factor time (posttest and follow-up).Normal distribution: Our primary outcome (the Behavioral Inattention Test) data will be analyzed after linear logistic transformation accordingly to the Rasch calibration, which ensures normal data distribution [39]. For the secondary outcomes, in the case normal distribution is not verified, a linear logistic transformation will be performed.In the case assumptions are verified, a mixed-model ANCOVA will be used with a 2 × 3 design, where the “between” factor will be the randomization group and the “within” factor will be the time of assessment, with the covariate pre-test baseline (T0) used to control for the LHN level before the beginning of the rehabilitation protocols.

In all cases, a two-tailed *t* test for independent samples will be employed to investigate the differences between groups. Data analysis will be performed using the MatLab (The Mathworks Inc.) and SPSS (version 13) softwares. We will accept a significance level of 5% (i.e., *p* value = .05) corrected for multiple comparisons when needed. Data from all randomized patients will be included in the analyses. Should data be missing at follow-up, data will be analyzed according to the intention to treat principle. However, participants will be contacted by telephone in the proximity of follow-up to ensure participant retention.

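### The sample-size calculation does not reproduce: it claims 80% power but uses the 90% constant, and its printed inputs give 22.9, not 25.2

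*Protocol article*

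**What the plan says.** The Sample size section of the protocol article bases the calculation on the Behavioral Inattention Test (BIT) and uses the standard formula for comparing two means, N = 2(z + z)²σ²/δ². Its inputs and results are:

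- error rates: "fixing *α* = 0.05 and 1 − *β* = 0.80";
- variance: "population variance established on previous studies [17] = 3.1";
- the denominator, printed under the symbol δ²: "absolute error allowed for parameter estimation = 2.84";
- constant and result: "10.5. The sample size resulting from the formula is 25.2";
- enrolment: "the minimum sufficient simple to reach our primary outcome was established as 56 subjects (28 per group"), "assuming a 10% loss at follow-up".

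The formula writes the first quantile at 1 − α, which is one-sided notation, and defines N as the trial's final size. Elsewhere, the Trial design section specifies a "2:2 randomized allocation ratio in a superiority trial design", that is, equal arms. The Statistical analysis section says that a "two-tailed *t* test for independent samples will be employed to investigate the differences between groups".

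**The concern.** The section prints a formula, every input and the answer, so it can be checked line by line, and it fails at two steps. The constant is not the one for the stated power, and the answer does not follow from the stated inputs. Two definitions are also wrong. N is described as the final size although this formula gives the number per group. δ is described as an allowed estimation error, although in a two-arm superiority comparison it is the treatment difference to detect.

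At stake is the quantitative justification for the primary endpoint. A reader cannot tell whether the target difference is √2.84 = 1.69 points or 2.84 points, whether the design power is 80% or 90%, or whether 56 really is the least that suffices. The last question has practical weight. The Trial status section reports recruitment from March 2019, an estimated completion of March 2021 and ten patients randomized. Anyone judging a shortfall in enrolment would look to the stated power and minimum.

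**Working it through.** **Inputs.** All come from the Sample size section unless noted: α = 0.05; power 0.80; constant 10.5; σ² = 3.1; δ² = 2.84; loss 10%; stated results 25.2 and 56 (28 per group). Equal allocation is from the Trial design section and the two-sided test from the Statistical analysis section.

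**1. The constant.** (z for α + z for power)², from unrounded quantiles:

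| α = 0.05 | 80% power | 90% power |
|---|---|---|
| two-sided | (1.960 + 0.842)² = 7.849 | (1.960 + 1.282)² = 10.507 |
| one-sided | (1.645 + 0.842)² = 6.183 | 8.564 |

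The printed 10.5 is the two-sided, 90%-power value. If α were one-sided, as the formula's notation suggests, 10.5 would imply about 94% power. Neither reading of α = 0.05 makes it an 80% constant.

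**2. The plan's own product.** 2 × 10.5 × 3.1 / 2.84 = 65.1 / 2.84 = 22.92. The stated 25.2 is not reproduced; the gap of about 10% is too large for rounding.

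**3. What could have produced 25.2.** Two routes come close:

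- 22.92 × 1.10 = 25.21. The 10% loss would then have been applied once here and again in going to 28, since 25.2 / 0.9 = 28.0.
- 3.1 is the SD and 2.84 the difference, both still to be squared: 2 × 10.5 × 9.61 / 8.0656 = 25.02. Then the labels σ² and δ² are wrong, and 25.2 may be a slip for 25.02.

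The text supports neither. The mixed readings are far off: 8.1 with 3.1 as variance and 2.84 as difference, and 71.1 with 3.1 as SD and 2.84 as squared difference.

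**4. Power actually obtained.** 28 per group less 10% leaves 25.2, so take 25 evaluable per arm. Two-sided t-test, noncentral t:

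| Reading | Standardized difference | Power at 25 per arm | Power at 28 per arm |
|---|---|---|---|
| variance and squared difference, as printed | √(2.84/3.1) = 0.957 | 91% | 94% |
| SD and difference | 2.84/3.1 = 0.916 | 89% | 92% |

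**5. What 80% power would need.** Two-sided, same formula with 7.849:

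- As printed: 2 × 7.849 × 3.1 / 2.84 = 17.1 per group; 17.1 / 0.9 = 19.0, or 18 / 0.9 = 20 if rounded up first. That is 20 per group, 40 in total.
- SD and difference: 2 × 7.849 × 9.61 / 8.0656 = 18.7 per group; 18.7 / 0.9 = 20.8, so 21 per group and 42 in total. Rounding up before inflating gives 19 / 0.9 = 21.1, so 22 per group and 44 in total.
- Sized by the t-test instead: 19 or 20 evaluable per group, hence 22 or 23 after loss, 44 or 46 in total.

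Against 56, the excess is 14 to 16 patients by the plan's formula without intermediate rounding, and 10 to 12 by the t-test.

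**The case against.** The strongest reply is that the slip does no harm to the trial. It errs on the safe side: 56 patients give about 90% power, so the trial is not underpowered, and nothing in the design, test or endpoint has to change. A single charitable reading also recovers most of the calculation. With 90% power, SD 3.1 and difference 2.84, the formula gives 25.02, and 25.02 / 0.9 = 27.8, so 28 per group and 56 in total. On that reading only the 0.80, the two labels and a possible misprint are wrong. The standardized difference barely depends on the reading (0.957 or 0.916), so power and N hardly move. Finally, no passage ties early closure to this calculation.

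Much of this stands. The claim that 56 exceeds the minimum is conditional on 80% being the intended power. The size of the excess depends on rounding and method, about 10 to 16 patients. Double counting of the loss is a possibility, not an established error. The descriptions of N and δ change no number, and the text itself goes on to use N per group. The link to early closure is an inference.

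It does not remove the point. The charitable reading needs the reader to overrule the stated power and both variable labels, with no support in the text. The raw target difference stays unknown. Nor is this detail left to another document: the article prints formula, inputs and answer, and they disagree.

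**Conclusion.** The concern holds. The constant 10.5 contradicts the stated 80% power, and the printed inputs give 22.9 rather than 25.2; no other section repairs either. The error is conservative. With 25 evaluable patients per arm the trial has about 91% power on the inputs as printed, or 89% if they are an SD and a difference. If 80% is the true intent, about 40 to 46 patients in total suffice for a two-sided test, depending on the reading and method, and calling 56 the minimum is wrong. If 90% was intended, 56 is about right and it is the stated power that is wrong.

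These figures assume equal arms, a two-sided 5% test, 10% loss, and that the plan's 3.1 and 2.84 are right in value. They are for a simple comparison of two means, as in the plan's formula, and take no account of baseline adjustment.

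**What to change.** Keep 56 and rewrite the Sample size section so that it reproduces:

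- State two-sided α = 0.05 with the quantile at 1 − α/2, and power of about 90% with the constant 10.5.
- Go back to the source of 3.1 and 2.84 and label each correctly: SD or variance, and between-group difference to detect or its square.
- Define N as the number per group and print the correct product: 22.9 if the present labels are right, 25.0 if the figures are an SD and a difference.
- Apply the 10% loss once. From 22.9 this gives 22.9 / 0.9 = 25.5, so 26 per group; 56 then exceeds the requirement, and the text should say so. From 25.0 it gives 27.8, so 28 per group.
- State whether the two figures are on the raw BIT or on the Rasch-transformed scale that the Statistical analysis section uses for the primary analysis.

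If 80% power is what was intended, state 7.85 and the smaller number that follows, and no longer call 56 the minimum. The cost is protocol wording only; no extra patients are needed.

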### Safety assessment

The stimulation protocol (i.e., the intervention) was devised accordingly to the guidelines for stimulation by Müri et al. 2013 [33]:
The application should be easy to implement without neuroimaging and neuronavigation systems for the localization of the target area. Many studies, as an alternative to neuronavigation, adopt the international 10/20 localization system.The total application time of the daily rehabilitation paradigm should not exceed ten sessions for 2 weeks. Indeed, protocols that provide everyday applications for more than 2 weeks are difficult to implement in rehabilitation centers and may not be tolerated by patients.

Indeed, when the r-TMS is administered according to the published international guidelines for brain stimulation protocols [33], it is a safe technique. The stimulation paradigm [17, 20] we will use in this study follows these guidelines. However, we will address any possible adverse events reported in the literature, as follows:
Mild headache after the session, usually not requiring any treatment (rather frequent). However, if requested by the patient, analgesics will be administered.Some local annoyance in the stimulated area (frequent): this effect rarely requires the suspension of r-TMS, but should the discomfort reported to be excessive, the session will be interrupted.Temporary loss of hearing (rare) for the duration of the stimulation session. In such a case, the session will be interrupted.Epileptic crises (actually rather rare) may occur in predisposed individuals. To minimize this risk, subjects who have suffered from seizures during the acute phase or have a diagnosis of epilepsy will be excluded from the trial (exclusion criterion). Moreover, it is planned to have the EEG track recorded during the neurophysiologic pre-test assessment to exclude epileptiform anomalies. If epileptiform abnormalities are present, the participant will be excluded from the trial. Finally, should a convulsive episode occurs during the 15 days of treatment with r-TMS despite the above precautions, the latter will be immediately suspended, and the patient will be treated according to the standard hospital protocols for epileptic seizures.

The PI will report any adverse event in an ad hoc CRF. Should the treatment (either intervention or sham control) be suspended, the reason for the suspension will be reported in the CRF. Data on adverse events will be analyzed appropriately and included in the study’s final report.

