### Assignment of interventions

#### Allocation

The PI will generate a blocked randomization list (2,2 per group) using the online software QuickCalcs (www.graphpad.com). Only the PI will have access to the randomization list after its generation.

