#### Blinding

To ensure a double-blind assessment, pre-treatment assessments (T0) will be performed before randomization, whereas post-test (T1) and follow-up (T2) assessments will be carried out by an assessor who will not be aware of the randomization group. The visual scanning protocol will be administered by therapists unaware of the patient’s allocation to intervention or control arms. Patients themselves will be instructed not to reveal any information to the assessors on the brain stimulation treatment received.

To minimize biases deriving from inter-rater measurement errors, the following interventions will be performed before the start of the trial:
Collegial assessments of patients who are not candidates for enrolment by the various assessors involved in the trial to standardize the administration modalities and resolve any discrepancies between scoring procedures.The subsequent development of an “assessment manual” containing all information for administering and scoring procedures.

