### Data collection and management

All data will be anonymized, and a specific alpha-numeric code will be attributed to each subject after enrolment. All the assessors will be responsible for transfers the data they have collected on paper CRF into the corresponding electronic CRF in the study database shortly after their collection. The study database is configured so that only the PI will be aware of all patient details, including the randomization group, and this information will not be visible to any of the assessors. Statistical analyses over the complete dataset will be performed at the end of data collection. However, interim analyses approved by the local ethical committee may be performed.

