### Oversight and monitoring

A dedicated member of the investigator team other than the PI will assess the completeness of data collection and be involved in monitoring all the clinical trial’s organizational, ethical, and scientific aspects. The PI will declare the end of the enrolment.

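### The only named reporter of adverse events is the investigator who holds the allocation list, and no blinded person has a role in recording or judging them

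*Protocol article*

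**What the plan says.** Four sections of the protocol article bear on this.

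- Safety assessment lists the expected effects of r-TMS: headache and local discomfort, both described as frequent to some degree, and temporary hearing loss and seizure, described as rare. It then says "The PI will report any adverse event in an ad hoc CRF". Adverse-event data are to be analysed and included in the final report; no method is named.
- Allocation has the PI generate the list and adds "Only the PI will have access to the randomization list after its generation".
- Data collection and management says "The study database is configured so that only the PI will be aware of all patient details, including the randomization group".
- Blinding covers two groups. At post-test and follow-up, "assessments will be carried out by an assessor who will not be aware of the randomization group". For the training, "The visual scanning protocol will be administered by therapists unaware of the patient’s allocation to intervention or control arms". Neither group is given a task concerning adverse events.

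The Discussion says that assessors and patients are blinded and presents this as reducing bias in general. It does not mention the PI. Under Control, sham is delivered by turning the coil to 90°, so whoever places the coil also knows the arm. The article does not name that operator.

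**The concern.** The two events that the article expects most often, headache and local discomfort, are subjective. Whether a mild complaint is entered, how severe it is judged to be, and whether it is put down to stimulation all depend partly on the person completing the form. The article itself lists these as known effects of r-TMS, so a reporter who knows the arm has a reason to expect them in one arm. The pull could also go the other way, since an investigator who hopes the treatment is well tolerated may discount mild complaints under active stimulation.

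What is at stake is how the safety section of the final report can be read. In a two-arm sham-controlled trial, event counts shown by arm will be taken as a comparison, whether or not a test is attached. The Conclusions section looks ahead to use in ordinary practice, where tolerability relative to sham is something readers will want to know.

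**Working it through.** The article states no figure on this point, so there is nothing to reproduce. The check sets out who knows the arm and who handles adverse events.

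| Person | Knows the arm? | Adverse-event role stated? |
|---|---|---|
| PI | Yes, for all patients (Allocation; Data collection and management) | Yes, reports events (Safety assessment) |
| Coil operator | Yes, for patients treated (follows from the 90° sham under Control) | None stated |
| Post-test and follow-up assessors | No (Blinding) | None stated |
| Visual scanning therapists | No (Blinding) | None stated |
| Team member under Oversight and monitoring | Not shown in the database; otherwise not stated | None stated; checks completeness of data |
| Patients | No (Discussion) | They experience the events; how they are asked is not stated |

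The only row with a stated adverse-event role is the one with full knowledge of allocation. This is an assignment that the article makes, not a gap that a fuller document could be expected to fill.

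**Illustration of the mechanism.** The true rates and recording probabilities below are assumed; none comes from the documents. Let the true rate p be equal in both arms, and let the probability that an event is recorded be d_R under r-TMS and d_S under sham.

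- Recorded rates are p × d_R and p × d_S.
- Spurious difference = p × (d_R − d_S). Spurious risk ratio = d_R / d_S.

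| p | d_R, d_S | Recorded, r-TMS vs sham | Difference | Risk ratio |
|---|---|---|---|---|
| 0.10 | 1.00, 0.90 | 10% vs 9% | 1 point | 1.11 |
| 0.30 | 0.90, 0.70 | 27% vs 21% | 6 points | 1.29 |
| 0.40 | 0.90, 0.50 | 36% vs 20% | 16 points | 1.80 |

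With 28 patients per group (Sample size), these differences are 28 × 0.01 = 0.28, 28 × 0.06 = 1.68 and 28 × 0.16 = 4.48 patients. For the largest, the standard error of the difference is √[(0.36 × 0.64 + 0.20 × 0.80) / 28] = √(0.3904 / 28) = 0.118, so 16 points is 0.16 / 0.118 ≈ 1.4 standard errors.

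**Exposure.** Seven stimulation sessions per patient (Intervention) × 28 patients = 196 planned sessions per arm. This counts occasions for recording. The percentages above are per patient, so the two should not be multiplied together.

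**The case against.** The case on the other side is substantial, and most of it limits how far the point can go.

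- **Reporting is not detecting.** A reader might infer that nobody but the PI notices or notes events. The article does not say so. With two centres, others may well observe events first. What stands is that the PI is the only reporter named.
- **Elicitation is not described.** A reader might infer from the Safety assessment section that events are captured mainly when patients complain, for instance from "should the discomfort reported to be excessive, the session will be interrupted". That wording governs the interruption of a session, and the similar wording on headache governs analgesia. Neither sets the rule for recording. Fixed questions may already be in the case report form, which is not shown, and an article commonly leaves that to other documents.
- **Collection is not open-label.** Patients are stated to be blinded, and they are the ones who perceive headache or discomfort. The exposure lies in recording and attribution by the PI.
- **Unawareness of deficits does not help the argument.** The Background describes lack of awareness of cognitive and motor deficits, not of pain, and randomization would spread it over both arms.
- **The Discussion's blinding claim is not a contradiction.** It names assessors and patients and concerns evidence of efficacy. It is merely broad enough to be read as covering safety.
- **Safety is not an endpoint,** and no between-arm test of adverse events is specified. The illustrated differences are also within chance at this sample size. Both are true. However, bias shifts the estimate whether or not a test would be significant, and the counts will still be read by arm.

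The presence of an unblinded coil operator means that the PI may not be the only unblinded person. That does not rescue the arrangement; it adds a second person who should not grade events.

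**Conclusion.** The point holds in a limited form. The article assigns adverse-event reporting to the holder of the allocation list and gives no blinded person any part in it, so the recording and attribution of headache and local discomfort by arm are open to observer bias. The documents do not allow the size or direction of that bias to be estimated; the range of 1 to 16 points shows the mechanism under assumed figures and is not a forecast. The conclusion rests on two assumptions: that adverse events will be shown by arm in the final report, and that no arm-blind grading is arranged elsewhere.

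The documents do not support the stronger reading that any difference, or absence of difference, in safety would be uninterpretable. Patients are stated to be blinded, and how events are elicited is unknown. The primary BIT result is unaffected. This is a cheap improvement worth making rather than a flaw that threatens the trial.

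**What to change.** 1. Record the events already listed under Safety assessment (headache, local discomfort, hearing change, seizure, other) with one short set of fixed questions. Put them in identical words in both arms after every stimulation session.
2. Repeat the questions at post-test and follow-up only after the outcome tests have been scored, so that the efficacy assessors do not hear stimulation-related complaints beforehand.
3. Have severity and relatedness graded before the arm is linked, by an existing team member who has no access to allocation and does not position the coil. The Oversight and monitoring section offers a candidate: "A dedicated member of the investigator team other than the PI will assess the completeness of data collection". The article does not confirm that this person meets both conditions, so that must be checked.
4. Leave the PI's clinical responsibility for events, and all rules on managing them, as they are.
5. In the Discussion, limit the blinding claim to efficacy assessment.

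The cost is a short form and a few minutes per session. Solicited questions will raise the recorded rate of mild events in both arms, and step 2 needs some discipline in scheduling. According to Trial status, ten patients had been randomized at the time of writing out of 56 planned, so 56 − 10 = 46 could still have been covered. Events in patients enrolled before the change should be reported separately from those collected afterwards.
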